**Funder**

Dexcom

This protocol describes the G-VAS study and provides information about procedures for entering participants. Every care was taken in its drafting, but corrections or amendments may be necessary. These will be circulated to investigators in the study. Problems relating to this study should be referred, in the first instance, to the Chief Investigator.

This study will adhere to the principles outlined in the UK Policy Frame Work for Health and Social Care Research. It will be conducted in compliance with the protocol, the Data Protection Act and other regulatory requirements as appropriate.

**Glossary of Abbreviations**

| CGM | Continuous Glucose Monitoring |
| --- | --- |
| GV | Glycaemic Variability |
| SD | Standard Deviation |
| MAG | Mean Absolute Glucose |
| NIHSS | National Institutes of Health Stroke Score |
| MRS | Modified Rankin Scale |
|  |  |
|  |  |
|  |  |
|  |  |
|  |  |
|  |  |
|  |  |
|  |  |
|  |  |
|  |  |
|  |  |
|  |  |
|  |  |
|  |  |
|  |  |
|  |  |
|  |  |
|  |  |
|  |  |
|  |  |
|  |  |
|  |  |
|  |  |
|  |  |
|  |  |
|  |  |

**Keywords**

Acute ischaemic stroke, diabetes, glycaemic variability

**Study Summary**

| **TITLE** | Glycaemic Variability in Acute Stroke |
| --- | --- |
| **DESIGN** | Observational cohort study |
| **AIMS** | Establish the impact of glycaemic variability on outcomes in acute stroke |
| **OUTCOME MEASURES** | **Glycaemic Primary outcome:** Mean absolute glucose (MAG) change during initial 72 hours after confirmed stroke  **Stroke Primary outcomes:** National Institutes of Health Stroke Scale (NIHSS) and Modified Rankin Scale (MRS) |
| **POPULATION** | N=200 with or without diabetes in 1:1 ratio |
| **ELIGIBILITY** | Acute Stoke (NIHSS>6) with or without diabetes |
| **duration** | Duration of hospital stay up to a maximum of 3 months. 1 year total duration. |

# 1. INTRODUCTION

## Background

People with diabetes who have a stroke have worse outcomes (Burton JK et al. 2019; Muir KW et al. 2011; Masrur S et al. 2015). Evidence for tight glycaemic control (e.g. maintaining blood glucose between 4.0 and ~7.5mmol/L) on the days immediately after stroke is lacking; studies have not shown improved outcomes and have noted higher rates of hypoglycaemia in intensively treated patients (Bellolio MF et al. 2014; American Heart Association. 2019). However the National Institute for Health and Care Excellence Guidance states that, ‘People with acute stroke should be treated to maintain a blood glucose concentration between 4 and 11mmol/L and hyperglycaemia (determined by both admission blood glucose and HbA1c) is associated with adverse outcomes (National Institute for Health and Care Excellence*.* 2017). In practice, maintaining blood glucose levels below 12mmol/L in people with acute stroke can be challenging, in particular when parental feeding is required.

Intermittent glucose measurement and measures of protein glycation provide limited information on the dynamic changes in glucose over time and do not take into account variability in glucose concentrations. Glycaemic variability (GV) is the consequence of multiple endogenous and exogenous factors and is a measurable variable.

To measure GV a data series of glucose values is required. These may be derived from continuous glucose monitoring and may be from within one time period (such as a day) or over several periods, allowing comparisons between periods. Initial methodologies for GV calculation were defined for self-monitoring data and newer methodologies have been expressly designed for continuous monitoring data.

There is no minimum length of time defined for satisfactory glycaemic variability calculation but, as with all statistical measures, the larger the dataset the more robust the metrics. Glucose concentration is not normally distributed about the mean. There is a long ‘tail’ to the glucose distribution extending into the hyperglycaemic range. Measures such as standard deviation do not take into account this asymmetric distribution and are thus relatively insensitive to hypoglycaemia. Hypoglycaemia is a significant barrier to improving glycaemic control and is a source of anxiety to people with diabetes. Not only that, it is unpleasant, is associated with morbidity and mortality and contributes to the global healthcare and financial burden of diabetes.

In vitro data has suggested that GV is more deleterious than consistent hyperglycaemia. Human umbilical vein endothelial cells exposed to a glucose concentration alternating between 5 and 20mmol/L every 24 hours show significantly more apoptosis than cells exposed to a constant concentration of 5mmol/L or 20mmol/L over 14 days (Risso A, et al. 2001). Using the same constant and alternating glucose concentrations in human umbilical vein endothelial cells overproduction of reactive oxygen species is highest with oscillating glucose concentrations (Quagliaro L, et al. 2003). In the same sequence of studies expression of the cytokine IL-6 was highest with oscillating glucose concentrations (Piconi L, et al. 2004).

In human proximal tubular cells exposed to increased glucose concentrations (25mmol/L), cell growth, collagen synthesis and cytokine production are elevated, and this is increased further by oscillating the glucose concentration between 25mmol/L and 6.1mmol/L (Jones SC, et al. 1999).

In the critical care scenario, where glucose control is considered important, even in people without diabetes, variability is associated with mortality. In 7049 critically ill subjects the SD of blood glucose concentrations was a significant independent predictor of mortality in the intensive care unit and in hospital (Egi M, et al. 2006). These data have been confirmed by other authors in 3250 subjects with a five-fold mortality increase between the lowest and highest quartiles of standard deviation (Calles-Escandon J, et al. 2010) and in 5728 patients in a study which demonstrated that high variability accompanied by a high mean glucose conferred the highest mortality (Hermanides J, et al. 2010). These data have also been shown in a paediatric intensive care unit where a retrospective review of 1094 patients showed that those in the highest quintile of glycaemic variability had a longer length of stay and significantly elevated mortality (Wintergerst KA, et al. 2006).

In people with stroke, GV has been investigated in people with and without diabetes using finger-prick glucose testing. Increased GV on day 1 after acute ischaemic stroke has been associated with poor functional outcome on hospital discharge but this effect was lost at 3 months follow-up (Camara-Lemarroy et al. 2016.). Early neurological deterioration in acute ischaemic stroke has also been associated with GV (Hui et al. 2018) In people without diabetes, more pronounced stress hyperglycaemic responses measured by continuous glucose monitoring over the initial 72 hours after acute stroke were associated with death or dependency at 3 months (Wada et al. 2018).

## 1.2 Rationale for current study

Increased glycaemic variability is associated with worse outcome in patients with diabetes after acute stroke.

## 1.3 Future Work

We subsequently plan to undertake a prospective randomised control trial utilising real-time continuous glucose monitoring in people with hyperacute stroke and diabetes, to determine if enhanced real-time measurement of glucose levels leads to reduced GV and, hopefully, better outcomes.

# 2. STUDY OBJECTIVES

**Primary Objective**

Establish the impact of glycaemic variability on outcomes in acute stroke in people with and without diabetes.

**Glycaemic Primary outcome:**

Mean absolute glucose (MAG) change

**Stroke Primary outcomes:**

Modified Rankin Scale (MRS) at 90 days

National Institutes of Health Stroke Scale (NIHSS) at 24, 48 and 72 hours

**Glycaemic Secondary outcomes:**

Number hypoglycaemic excursions,

Time (minutes and %) spent in hypoglycaemia (<3.9mmol/L, 70mg/dL)

Time spent in hypoglycaemia (<2.8mmol/L, 50mg/dL)

Time spent in hypoglycaemia (<3.3mmol/L, 60mg/dL)

Time in euglycaemia (3.9-7.8mmol/L, 70-140mg/dL)

Time spent in target (3.9-10mmol/L, 70-180mg/dL)

Time spent in hyperglycaemia (>10mmol/L, 180mg/dL)

Severe hypoglycaemia (3rd party assistance required)

MAD%,

MARD%

Glucose variability, measured by Mean absolute glucose (MAG) and Low blood glucose index (LBGI)

HbA1c and other markers of metabolism

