## 6.2 Enrollment and study conduct

Following informed consent/assent the research team will collect full medical and medication history, as well as historic bloods from Cerner (hospital computer system) as per routine clinical care. In addition to the admission blood tests, venous blood (<20 ml) will be taken on admission and at 24 and 72 hours for measurement of biochemical, metabolic and hormonal profiles (including, but not limited to: glucose, HbA1c, c-peptide, CRP and other markers of neuro-inflammation). Blood samples (whole blood and plasma) will be stored temporarily in a -20 degree freezer (frozen within 24 hours) at Charing Cross Hospital and transported in bulk by courier on dry ice to a -80 freezer at St Mary Hospital for the use in future research. If participants meet the inclusion criteria they will be enrolled on to the study immediately.#

We do not anticipate that any significant incidental findings will arise as the data pulled from Cerner will be retrospective and much of the sample analysis is done post-hoc. If participants in the “non-diabetes” cohort return blood results that indicate that they have diabetes we will inform their clinical team so that they can manage this appropriately.

Blinded continuous glucose monitoring (CGM) will be applied to 100 consecutive volunteers with an acute stroke (NIHSS score >6) and a previous diagnosis of diabetes who are admitted to Charing Cross Hospital and 100 people with an acute stroke (NIHSS score >6) without diabetes in a 1:1 ratio. This will be done as soon as is feasible after admission. Clinical team will be instructed to test participants capillary blood glucose as per standard care, and if symptoms of hypo- or hyperglycaemia occur. Sensors will be worn for a maximum of 10 days (whilst in hospital) but will be removed on hospital discharge should this occur before 10 days are up. Glucose alerts will not be enabled as the CGM will be blinded.

CGM involves insertion of a small plastic cannula to the subcutaneous tissue of the abdominal skin by members of the study team. The cannula is attached to a small data logger which will be taped to the patients’ skin. CGM will take place for 10 days, throughout the participants stay in hospital.

If the participants’ sensor fails or falls out the research team will provide a new sensor and will help the participant to insert it. .

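### The count of hypoglycaemic excursions and the minutes below 3.9 mmol/L are raw totals over a sensor wear time that ends at discharge or day 10, with no rate, common window or exposure adjustment

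*Protocol*

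**What the plan says.** Section 2 of the protocol (Glycaemic Secondary outcomes) lists "Number hypoglycaemic excursions" with no rate, denominator or time window. The next line is "Time (minutes and %) spent in hypoglycaemia", for the 3.9 mmol/L threshold. It is the only time line that names a unit, and it names two. The lines for <2.8, <3.3, 3.9-7.8, 3.9-10 and >10 mmol/L give neither a unit nor a window.

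Section 6.2 sets the observation time: "Sensors will be worn for a maximum of 10 days (whilst in hospital) but will be removed on hospital discharge" if that comes before day 10. Monitoring starts as soon as feasible after admission, so the start is not fixed either.

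The Study Summary ties the first 72 hours to mean absolute glucose (MAG) change, the glycaemic primary outcome. No window is tied to the secondary glucose outcomes. Length of hospital stay is itself listed under Other Secondary outcomes. For analysis, section 7 names an independent t-test for parametric data and a Mann-Whitney test for non-parametric data between groups, and says nothing about exposure time.

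**The concern.** A count, or a number of minutes, accumulates for as long as the sensor is worn. Wear stops at discharge, so two patients with the same glucose behaviour get different totals if one goes home sooner. A comparison of totals then mixes glycaemia with length of stay.

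This matters because stay is unlikely to be neutral in this study. The protocol's background says that people with diabetes do worse after stroke, and the primary objective is to relate glycaemia to outcome. A glycaemic measure that partly counts days in hospital carries some of the outcome inside the exposure. Section 7 intends the data as pilot data for a larger randomised trial, so a count driven by wear time could also mislead the planning of that trial.

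**Working it through.** The protocol has no figure of its own to reproduce: it states no power calculation, significance level, excursion rate or expected stay.

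**1. Arithmetic for two patients**

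From section 6.2: wear of up to 10 days. Assumed: a shorter wear of 3 days, 0.5 excursions per day, and 5% of time below 3.9 mmol/L, the same in both patients.

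- Expected count = rate × days: 0.5 × 3 = 1.5 against 0.5 × 10 = 5.0.
- Minutes below 3.9 = proportion × 1,440 × days: 0.05 × 1,440 × 3 = 216 against 0.05 × 1,440 × 10 = 720.
- Both ratios are 10/3 = 3.3, whatever rate or proportion is assumed. The percentage is 5% in both patients.

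**2. Effect on a two-group comparison**

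From the protocol: 100 participants per group and the Mann-Whitney test. Assumed: a two-sided 5% level; exponential length of stay, with wear held between 1 and 10 days; a mean of 0.5 excursions per day with gamma variation between patients (shape 1) and Poisson counts. Glycaemia is identical in both groups, so every rejection is a false positive. There were 2,000 simulated studies per row.

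| Mean wear, days | Ratio of expected counts | Raw count | Count per day of wear |
|---|---|---|---|
| 5.4 v 5.4 | 1.00 | 4.3% | 5.4% |
| 5.4 v 4.7 | 5.39/4.70 = 1.15 | 10.5% | 5.9% |
| 5.8 v 4.4 | 5.78/4.42 = 1.31 | 23.6% | 6.8% |
| 6.4 v 4.4 | 6.35/4.43 = 1.43 | 45.7% | 8.3% |

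The simulation standard error near 5% is √(0.05 × 0.95/2,000) = 0.5 percentage points, so 4.3% is compatible with 5%.

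A second set of assumptions (gamma-distributed wear, 4,000 simulations, 0.5 or 1 excursion per day) gave 17-20% for raw counts at mean wear of 6.8 v 5.6 days, and 28-33% at 7.2 v 5.6 days.

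**3. Minutes against per cent**

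This was simulated for time in target, with a mean of 70% (Beta(7,3)). In the same four wear scenarios, minutes rejected in 5.1%, 27.8%, 73.5% and 96.3% of studies. The percentage rejected in 4.5-5.2%. These figures show what follows if that line is analysed in minutes, which the protocol does not say. Minutes below 3.9 mmol/L were not simulated; for them only the ratio in step 1 applies.

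**4. Check of the remedy**

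Counts within a fixed 72 hours, fully observed in everyone, rejected in 5.0%. Counts per day of wear, compared by Mann-Whitney, are far better than raw counts but drift to 8.3% when wear differs most. Shorter wear gives a more discrete rate with more zeros, so the two distributions differ in shape even when the mean rate is the same.

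**The case against.** The strongest reply is that section 2 is a list of outcome names. The window, the valid-wear denominator and any scaling per 24 hours are details that an analysis plan often supplies, and section 7 does not say which outcomes are tested or in what form. That stands in part: nothing in the protocol forbids a rate. But it does name a count and a number of minutes, sets a wear time that varies by patient, and names only tests that ignore wear. Followed as written, it compares totals that scale with stay.

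A reader might infer more than this, and the documents do not support it:

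- **That all the time outcomes are raw minutes.** Only the 3.9 mmol/L line mentions minutes, and it gives the percentage beside them. Lines such as "Time spent in target (3.9-10mmol/L, 70-180mg/dL") and "Time in euglycaemia (3.9-7.8mmol/L, 70-140mg/dL") name no unit, and the per cent on the first time line may be meant to carry down the list.
- **That totals will be too high in diabetes or in poor outcome.** Sicker patients may stay longer, but early death shortens wear. Section 6.1 puts early mortality after acute stroke at about 10%, and section 6.2 does not discuss death. The bias could run either way.
- **That the false-positive rate is known.** The protocol gives no lengths of stay. With equal wear the between-group test is not inflated.

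It is also fair that a 72-hour window does not by itself equalise exposure, because sensors start at varying times and some patients may leave early.

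**Conclusion.** The point holds for the number of hypoglycaemic excursions and for the minutes version of time below 3.9 mmol/L. Both are totals over a patient-specific wear time, and the plan makes no allowance for that time. The 3.3-fold ratio between 10 and 3 days of wear is plain arithmetic at a constant daily rate. The false-positive rates of 10.5% to 45.7% for counts rest on assumed differences of about 0.7 to 1.9 days in mean wear, an assumed event rate and an assumed 5% level. They show what a difference in stay would do and do not predict what will happen.

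The percentage below 3.9 mmol/L is not affected, nor is MAG over 72 hours. For the remaining time lines the accurate criticism is that unit and window are unstated. The consequences are limited to secondary outcomes of a study that describes itself as hypothesis generating and not fully powered. The correction is still worth making, because it is nearly free.

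**What to change.** - Define the excursion outcome as the number per 24 hours of valid CGM time. Compare groups preferably with a count model that allows for overdispersion and has log valid-wear time as offset. A common window, such as the 72 hours already used for MAG, is the alternative; valid time within it should still be the denominator, because start and discharge times differ.
- Make the percentage of valid CGM time the compared measure for every threshold and range in section 2.
- Keep raw minutes and whole-wear totals as descriptive results, shown with the distribution of valid wear time in each group.

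The cost is a few lines in the protocol or the analysis plan. It uses the same CGM data and adds no burden for patients. There are two small downsides: rates from short wear are noisy, and a 72-hour window uses fewer events than the full wear period.

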**Stroke Secondary outcomes:**

Barthel Index (BI)

Stroke Impact Scale (SIS)

Pneumonia or infection requiring antibiotic treatment

All cause vascular events (MI, stroke recurrence etc) during first 14 days

Requirement for enteral feeding and duration of enteral feeding

**Other Secondary outcomes:**

Mortality at 90 days

Length of hospital stay

Readmission to hospital

Renal complications

Escalation to High Dependency Unit or Intensive Care Unit

## 3. STUDY DESIGN

This will be an observational cohort study.

100 consecutive volunteers with an acute stroke (NIHSS score >6) and a previous diagnosis of diabetes who are admitted to Charing Cross Hospital Hospital and 100 people with an acute stroke (NIHSS score >6) without diabetes will be recruited in a 1:1 ratio.

Each participant will remain in the study for the duration of their stay in hospital, up to a maximum of 3 months. 1 year total duration for active recruitment and study conduct.

# 4. Participant Entry

## 4.1 Pre-registration evaluations

NIHSS Score (this should be greater than 6). Participants will have been admitted to hospital for an acute stroke.

## 4.2 Inclusion Criteria

- Known Diabetes **or** HbA1c >42 **or** no known diabetes
- Clinically suspected ischaemic stroke (NIHSS score >6) within 12 hours of symptoms
- Adults ≥18 years of age

## 4.3 Exclusion Criteria

- Haemorrhagic stroke
- Unable to participate due to other factors, as assessed by the Chief Investigators
- Pregnancy
- Premorbid MRS >2
- Adult over 80 years of age
- Known to have a terminal condition or conditions that suggest a life expectancy less than 1 year

## 4.4 Withdrawal criteria

- The subject has a serious event related to study
- Investigator initiated discontinuation of study due to participation or equipment concerns
- Withdrawal of consent/assent

Withdrawal will be immediate. Identifiable data already collected with consent will be retained and used in the study. No further data would be collected or any other research procedures carried out on or in relation to the participant.

If a participant is unable to provide verbal consent, assent will be sought from their carer, In line with the Mental Capacity Act 2005 (MCA) which covers research involving adults (aged 16 years and over) who lack capacity in England and Wales. If the participant regains capacity consent will be sought. In this instance, if the participant does not consent to be on the study they will be withdrawn and all data will be destroyed.

Participants who lack capacity at the time of their enrollment into the study will further be withdrawn if:

- they indicate in any way that they want to be withdrawn from the project (for example, if they become upset or distressed)
- any of the Act’s requirements are no longer met.

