## 8.2 Consent

Consent to enter the study must be sought from each participant only after a full explanation has been given, an information leaflet offered and time allowed for consideration. Signed participant consent should be obtained. The right of the participant to refuse to participate without giving reasons must be respected. After the participant has entered the study the clinician remains free to give alternative treatment to that specified in the protocol at any stage if he/she feels it is in the participant’s best interest, but the reasons for doing so should be recorded. In these cases the participants remain within the study for the purposes of follow-up and data analysis. All participants are free to withdraw at any time from the protocol treatment without giving reasons and without prejudicing further treatment. Refer to section on recruitment and consent for further details.

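### Section 4.4 does not separate stopping study procedures from leaving follow-up, so the 90-day MRS and mortality go uncollected in participants who have not withdrawn consent

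*Protocol*

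**What the plan says.** Section 4.4 of the protocol opens with three triggers:

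- "The subject has a serious event related to study"
- "Investigator initiated discontinuation of study due to participation or equipment concerns"
- "Withdrawal of consent/assent"

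One consequence follows for all of them. Withdrawal takes effect at once, earlier data are kept ("Identifiable data already collected with consent will be retained and used in the study"), and from then on "No further data would be collected or any other research procedures carried out on or in relation to the participant". The section has no category for a participant who stops the sensor or blood sampling but stays in follow-up.

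Two further rules in section 4.4 concern capacity. A participant enrolled without capacity is withdrawn on any sign of wanting to leave, or if the Mental Capacity Act requirements cease to be met. For someone who regains capacity, "if the participant does not consent to be on the study they will be withdrawn and all data will be destroyed". These rules are not in question here.

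Section 2 makes MRS at 90 days and NIHSS at 24, 48 and 72 hours the stroke primary outcomes, and lists 90-day mortality as a secondary outcome. The Study Summary sets the MAG window at the first 72 hours. Section 6.2 allows sensor wear for up to 10 days in hospital. Section 6.3 obtains MRS by telephone for those discharged within 3 months.

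**The concern.** Only one of the three triggers is a refusal. In the other two the investigator or an event ends participation, and the participant may be quite willing to answer a telephone call at 90 days. Applying the consent rule to them gives up a primary outcome for a reason unrelated to whether it could be obtained.

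The study exists to relate early glycaemic variability to stroke outcome. A participant with a complete 72-hour MAG but no 90-day MRS contributes nothing to that relation. Because the rule governs what is collected, the gap cannot be repaired at analysis except by imputation.

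The loss might also be selective. Participation concerns are not defined in the protocol and could plausibly arise more often in agitated or more impaired patients. Section 6.1 expects about one third of eligible patients to be unable to engage with consent because of the stroke.

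**Working it through.** **1. No figure to reproduce.** The protocol states no withdrawal rate, dropout allowance, effect size or power, and section 7 describes the study as hypothesis-generating and not fully powered. The main check is therefore a reading of the text. The arithmetic in steps 3 and 4 only illustrates scale.

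**2. What each trigger costs under the text as written.**

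| Trigger (section 4.4) | Participant has refused? | Further data | 90-day MRS and mortality |
|---|---|---|---|
| Study-related serious event | No | None | Not collected |
| Participation or equipment concern | Not necessarily | None | Not collected |
| Withdrawn consent or assent | Yes | None | Not collected, rightly |

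Timing example: on day 6 of a 10-day wear period, the 72-hour MAG window (3 days) has closed and the 24-, 48- and 72-hour NIHSS scores are due and retained. What is lost is everything still to come, chiefly the 90-day MRS and mortality. If withdrawal comes before 72 hours, any remaining NIHSS scores are lost too.

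**3. Shift in a poor-outcome proportion.** N = 200 is from the Study Summary. The remaining inputs are assumptions: w, the share withdrawn under the first two triggers; P = 50%, the true poor-outcome proportion; and p_w, the proportion among those withdrawn.

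Observed proportion = (P − w·p_w)/(1 − w); bias = observed − P.

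Example: w = 5%, p_w = 70% gives (0.50 − 0.035)/0.95 = 0.4895, a bias of −1.05 points.

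| w | Left with MRS | p_w = 50% | p_w = 70% | p_w = 90% |
|---|---|---|---|---|
| 2% | 196 | 0 | −0.41 | −0.82 |
| 5% | 190 | 0 | −1.05 | −2.11 |
| 10% | 180 | 0 | −2.22 | −4.44 |

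(Bias in percentage points.)

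**4. Loss of precision.** The 95% half-width is 1.96·√(0.25/n): 6.9 points at n = 200, and 7.0, 7.1 and 7.3 points at n = 196, 190 and 180. For two groups of 100 and an assumed difference of 0.4 SD (two-sided 5%), power is 80.7%. It falls to 80.0%, 78.7% and 76.5% with 98, 95 and 90 per group, taking losses as equal in the two groups.

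**5. What this does not show.** Step 3 concerns a marginal proportion. Bias in the MAG–MRS association depends on whether loss is related to MRS beyond what MAG and any other modelled variables explain. The protocol gives nothing from which to estimate that.

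**6. After the change.** If outcomes are still collected after the first two triggers, w from those causes is 0, and so are the bias and the loss of precision from them, apart from participants who cannot be reached.

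**The case against.** The strongest objection is that these withdrawals should be few and unrelated to prognosis. Section 5.2.2 treats an event as related only if it resulted from research procedures, which in section 6.2 are a blinded subcutaneous sensor and small blood samples. Stroke death and relapse are not reported as SAEs. Ordinary sensor trouble is handled by replacement: if a sensor "fails or falls out the research team will provide a new sensor". If withdrawal is unrelated to outcome the bias is zero, and the study does not claim full power. This stands as an argument about size. It does not justify losing a primary outcome when nobody has refused it.

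Two contradictions might be inferred, and the documents support neither.

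- **Section 6.2.** Replacing a failed sensor can coexist with a right to discontinue over a concern that replacement does not resolve.
- **Section 8.2.** The sentence "In these cases the participants remain within the study for the purposes of follow-up and data analysis" refers to a clinician giving alternative treatment, not to withdrawn participants. It shows that the protocol accepts follow-up after a departure from plan, but it does not contradict section 4.4.

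A third objection is partly right: a participation concern may be reluctance or distress short of formal withdrawal, and continued follow-up would then be wrong. The change must therefore exclude any case with a sign of objection. Nor is the telephone call a guarantee. Section 6.3 provides it only for those discharged within 3 months, and section 6.1 may require a consultee to answer.

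**Conclusion.** The point holds as a flaw in the data-collection rule and should be corrected. As written, section 4.4 leaves participants who have not withdrawn consent without a 90-day MRS or 90-day mortality, for reasons that do not prevent collection.

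The size is unknown and probably modest. In the illustration the shift runs from 0 to 4.4 points, and the larger values need both 10% withdrawal and a 90% poor-outcome rate among those withdrawn. Every input except N = 200 is assumed.

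A reader might go further in three ways that the text does not support:

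- **Loss tied to severity.** This is possible, most plausibly through participation concerns, but the protocol does not show it for any of these triggers.
- **Data thrown away.** Earlier data are kept and the later outcome is simply not collected. Destruction applies only to a participant who regains capacity and then declines.
- **Safety reporting ended.** Section 5.2.2 still requires the SAE form within 24 hours, ethics committee reporting of related and unexpected events within 15 days, and notification of the sponsor, with no exemption for withdrawn participants.

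**What to change.** Split section 4.4 into two categories.

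**(a) Discontinuation of study procedures:** an equipment concern, a study-related serious event, or an investigator decision without any objection from the participant or consultee. CGM and study blood sampling stop, and data to that point are kept. Any remaining NIHSS scores, clinical events, 90-day MRS and 90-day mortality are still collected while consent or consultee agreement stands.

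**(b) Withdrawal from the study:** withdrawn consent or assent, any sign of objection or distress, or Mental Capacity Act requirements no longer met. No further data are collected, as now written. The rule for a participant who regains capacity and declines is unchanged.

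The cost is a short amendment to section 4.4, matching wording in the participant and consultee information sheets, and some extra follow-up contacts. At the assumed 2–10% withdrawal that is 4 to 20 people (200 × 0.02 to 200 × 0.10), mostly reached by the call that section 6.3 already provides.
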